### Sample size {14}

The sample size calculation is based on the primary endpoint, CCI within 30 days after surgery. Assumptions are based on the literature: a decrease of the CCI by 10 points is considered relevant by patients and clinicians and a conservative standard deviation of 20 is assumed [1]. Based on a *t*-test with a two-sided significance level of *α*=0.05, a sample size of *n*=128 patients (64 per group) has to be recruited to achieve a power of 80% to reveal this difference. The primary endpoint will be analysed by a linear mixed regression model which leads to equal or even increased power as compared to using a two-sided *t*-test (see the “Statistical methods” section for further detail). To compensate for “intraoperative drop-outs” (10%; decision for no tumour resection) and “postoperative drop-out” and “loss to follow-up”, further 15% of patients will be randomized leading to a total sample size of *n*=152 (76 per group). The number of patients to be screened (*n*=304 to be assessed for eligibility; 304 × 0.5 = 152) was calculated with an assumed 50% of patients participating and meeting the inclusion and exclusion criteria (Fig. 1).

### Recruitment {15}

To enrol the required number of patients in the planned recruitment period, 8 trial sites will participate in this trial. The trial will be performed by the Clinical Trial Network of the German Society of Surgery (CHIR-*Net*, www.chir-net.de). For a full list of participating centres, please see Supplement 1. Recruitment will start in March 2023 and run until February 2025. All patients with oesophageal cancer in the participating hospitals will be screened and asked to participate in the trial.

## Assignment of interventions: allocation

### Sequence generation {16a}

To ensure equal distribution of patient characteristics randomization will be used. Allocation of treatments will be performed using a web-based randomization tool (www.randomizer.at). Block-wise randomization of variable block sizes will be conducted. Randomization will be performed preoperatively for practicality reasons. Randomization will be stratified by centre.

### Concealment mechanism {16b}

Randomization will be performed preoperatively as planning, positioning and operative set-up differ between MIN-E and HYBRID-E. Block size will be kept confidential to the study team.

### Implementation {16c}

Randomization will be performed by a study team member before surgery. Names of the randomizing study team member as well as the operating surgeons will be noted. They will not be involved in outcome assessment.

## Assignment of interventions: blinding

### Who will be blinded {17a}

The following blinding measures will be implemented in the trial according to current recommendations [28]:A.Patients will not be informed about the randomization result for the first 7 postoperative days (till after visit 5) to ensure blinding for the early postoperative period. They will be blinded with a large chest dressing until after visit 5 [3]. As the abdominal access is minimally invasive in both groups, no special blinding measures are needed for the abdomen. Accordingly, subjective outcomes prone to detection bias such as quality of recovery assessed on postoperative day (POD) 4 and POD 7 and pain at rest and during movement assessed on POD 2, 4 and 7 will be assessed while patients are still blinded. Long-term blinding of patients is not feasible, since unblinding during a change of wound dressings or during inspection of the wound is likely. However, most endpoints including the primary endpoint CCI are assessed according to objective criteria (e.g. reoperation, ICU stay, death) and are thus not affected by unblinding.B.Surgeons performing the operation are unblinded to the trial intervention. Consequently, surgeons who have performed the operation should not act as outcome assessors to avoid influencing the primary endpoint.C.Similarly, blinding of the treating team is not feasible, since unblinding during change of wound dressings would be likely. Again, endpoints other than the above-mentioned PROMs (pain, QoR) are not affected by unblinding as they are assessed according to objective criteria (e.g. reoperation, ICU stay, death) and are thus not affected by unblinding.D.Blinding of outcome assessors is not necessary as endpoints other than the above-mentioned PROMs (pain, QoR) are not affected by unblinding as they are assessed according to objective criteria (e.g. reoperation, ICU stay, death) and are thus not affected by unblinding.

The trial statistician will perform the analyses according to a predefined statistical analysis plan which will be finished prior to database closure.

### Procedure for unblinding if needed {17b}

If unblinding of the patient is necessary in the first 7 postoperative days, this can be done by the unblinded study personnel or the treating physicians.

## Data collection and management

### Plans for assessment and collection of outcomes {18a}

See the section “Outcomes {12}”. The trial will be performed by the Clinical Trial Network of the German Society of Surgery (CHIR-*Net*, www.chir-net.de). The CHIR-*Net* has successfully performed trials with similar indications and recruitment rates. All trial sites have already successfully participated in surgical clinical trials and have the necessary expertise, equipment and personnel to perform this trial.

### Plans to promote participant retention and complete follow-up {18b}

In order to minimize loss to follow-up, the following measures have been implemented:A pragmatic trial design with high-external validity, meaning that trial sites will have little problems to adapt their standard clinical workflow to the follow-up visitsThe follow-up visits after discharge can be performed via telephone if patients are unable to attend an outpatient appointmentAll trial sites are trained in performing surgical clinical trials (CHIR-Net) and have successfully participated in similar trialsOnly high-volume trial sites committing to include at least 10 patients per year will be chosen as trial sites. The sites must perform 26 or more oesophagectomies annually.

### Data management {19}

All protocol-required information collected during the trial must be entered by the investigator, or designated representative, in the eCRF. The investigator, or designated representative, should complete the eCRF pages as soon as possible after information is collected, preferably on the same day that a trial subject is seen for an examination, treatment or any other trial procedure. Any outstanding entries must be completed immediately after the final examination. An explanation should be given for all missing data. Protocol deviations become clear via documentation in the eCRF and will be listed by the data management. Further protocol deviations are explicitly asked for in the eCRF and have to be described by trial centres. The completed eCRF must be reviewed and signed by the investigator named in the trial protocol or by a designated sub-investigator. The Heidelberg Institute of Medical Biometry (IMBI) is responsible for the data management within the trial. The study data will be collected and managed using REDCap (Research Electronic Data Capture) [29], a secure, web-based data capture application hosted at the IMBI. To assure a safe and secure environment for data acquired, data transmission is encrypted with secure socket layer (SSL) technology. Only authorized users are able to enter or edit data, and the access is restricted to data of the patients in the respective centre. All changes to data are logged with a computerized timestamp in an audit trail. All data will be pseudonymized. To guarantee high data quality, data validation rules will be defined in a data validation plan. Completeness, validity and plausibility of data will be checked in time of data entry (edit-checks) and using validating programs, which will generate queries. If no further corrections are to be made in the database, eCRF data will be locked. Data will finally be downloaded and used for statistical analysis. All data management procedures will be conducted according to written defined standard operating procedures (SOPs) of the IMBI that guarantee an efficient conduct complying with GCP. At the end of the study, the data will be transformed into different data formats (e.g. csv-files) for archiving and to ensure that it can be re-used.

### Confidentiality {27}

All information on study participants will be retained in password-protected files and locked cabinets at the Clinical Trials Centre. To ensure confidentiality, participants will be allocated an individual trial identification number. Access to this information will only be provided to immediate study staff, unless required by legislative or regulatory agencies.

### Plans for collection, laboratory evaluation and storage of biological specimens for genetic or molecular analysis in this trial/future use {33}

No biological samples are collected.

## Statistical methods

### Statistical methods for primary and secondary outcomes {20a}

For the examination of the primary endpoint, CCI within 30 days after surgery, the hypotheses to be assessed in the primary analysis are as follows:

H0: μ1 = μ2 vs H1: μ1 ≠ μ2, where μ1 and μ2 denote the mean CCI in the control and intervention groups respectively.

The confirmatory analysis of the primary efficacy endpoint corresponds to the primary estimand. Only patients who underwent oesophagectomy will be included in the primary analysis (drop-out assumed to be less than 10%) and they will be analysed in the group they were randomized (converted patients remain in their group). This reflects an analysis according to a modified intention-to-treat principle and the derived dataset is referred to as the mITT. The level of significance is set to 5% (two-sided).

The mean differences of the CCI will be examined using a linear mixed model including treatment group and adjusting for age as a fixed effect, as well as center as a random effect. Due to the stratified randomization and relatively large number of centers in relation to the sample size, inclusion of centre as a random effect is recommended [24]. The correlation matrix will have a variance components structure. The primary analysis will be performed after data for the primary endpoint is available for all patients. The database will be closed before the analysis of the primary endpoint.

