If another type of surgery (other than abdominal and right thoracic oesophagectomy, Ivor-Lewis procedure) is indicated for complete tumour resection (e.g. transhiatal extended gastrectomy or abdomino-cervical oesophagectomy), the patient remains in the trial and will be followed up for the entire trial period. This is meaningful, because these types of surgeries constitute major operations, are associated with major complications and oncological outcome parameters can be analysed. The MICkey trial randomization will occur preoperatively, as intraoperative randomization is impractical due to the need for different operative set-ups (e.g. preparation of robot/laparoscopic towers) and patient preparation. To minimize bias, two intraoperative exclusion criteria have been defined. As a consequence, intraoperative exclusion of previously randomized patients might occur:*Case 1 (intraoperative diagnosis of previously occult metastases that prohibit surgical resection according to current S3 guidelines)* [19]: In this case, patients in both groups will undergo diagnostic laparoscopy only, as the abdominal part of the operation is the same in both groups and will be performed minimally invasive in both groups. Diagnostic laparoscopy is a minor surgery, with very few associated complications. Consequently, follow-up for the primary endpoint (comprehensive complication index) makes no sense, as it adds nothing to answering the primary research question, namely which surgical technique is associated with less complications after oesophagectomy, an operation which is associated with major complications. In addition, almost all secondary endpoints are meaningless in patients undergoing diagnostic laparoscopy only. Therefore, these patients will be excluded from the study. These patients will be defined as “intraoperative drop-out”. However, in line with the current S3 guidelines [19], patients with newly diagnosed intraoperative “sehr limitierter Fernmetastasen” (very limited metastases), which are “gut resektabel” (easily resectable), oesophagectomy in combination with resection of this “kleine, gut resektable Metastase” (small, well-resectable metastasis) should be performed [9] (recommendation 8.13). In this case, the patient remains in the trial and is regularly followed up.*Case 2 (tumour resection technically impossible)*. As for case 1, follow-up of patients makes little sense as these patients will undergo minor surgery only and DFS cannot be measured. Again, these patients will be defined as “intraoperative drop-outs”.The occurrence of both cases (case 1 and case 2) is assumed to be equally distributed between both study groups.

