#### Population

The targeted population is defined through the inclusion and exclusion criteria (incl. intraoperative exclusion criteria).

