#### Intercurrent events (ICE)

Specific events (e.g. death, re-operation) which can occur after randomization will be handled within the primary endpoint definition reflecting a composite strategy. Intraoperative deaths will be graded as grade V complication according to Dindo-Clavien. Treatment switcher from laparoscopic/robotic to open can occur and will be handled according to the intention-to-treat principle (treatment policy approach). Other intraoperative events can lead to an exclusion from the population (see intraoperative exclusion criteria).

Other post-randomization events will not be considered. This reflects a treatment policy approach, which means estimating the effect of randomized treatment irrespectively of other post-randomization events not captured in the primary endpoint definition.

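### The primary analysis set, limited to patients who underwent oesophagectomy, is narrower than the estimand it is said to match, and the reasons for one intraoperative exclusion are secure only in the shared abdominal phase

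*Protocol article*

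**What the plan says.** **Analysis set.** Statistical methods {20a} states: "The confirmatory analysis of the primary efficacy endpoint corresponds to the primary estimand". The next sentence gives the rule: "Only patients who underwent oesophagectomy will be included in the primary analysis (drop-out assumed to be less than 10" (per cent). Patients are analysed as randomised, converted patients stay in their group, and the set is called the mITT.

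**Estimand.** Under Population: "The targeted population is defined through the inclusion and exclusion criteria (incl. intraoperative exclusion criteria". Under Intercurrent events: "Intraoperative deaths will be graded as grade V complication according to Dindo-Clavien". Conversions follow treatment policy, and so do remaining events outside the endpoint definition: "This reflects a treatment policy approach, which means estimating the effect of randomized treatment irrespectively of other post-randomization events". The same section allows other intraoperative events to lead to exclusion and points to the intraoperative criteria. Eligibility {10} lists two: (a) occult metastases that prohibit resection, and (b) technically impossible resection.

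**Handling during surgery.** Section {11b} covers patients who need a different operation: "transhiatal extended gastrectomy or abdomino-cervical oesophagectomy), the patient remains in the trial and will be followed up for the entire trial period". It justifies this by noting that such operations are major and carry major complications. Patients under (a) have a diagnostic laparoscopy only and leave the study. For (b) the reason given is: "follow-up of patients makes little sense as these patients will undergo minor surgery only and DFS cannot be measured". Both cases are assumed to occur equally often in the two groups.

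**The concern.** The set in {20a} is defined by the operation received. The estimand population is defined by two named exclusion criteria. A patient can fail the first definition without meeting either criterion. For such a patient the claimed correspondence between analysis and estimand does not hold, and the set depends on which section the statistician follows. A death on the table is among the worst outcomes the trial can record, so it should not depend on wording.

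The second issue is criterion (b). Excluding patients after randomisation does little harm when the decision is made before the arms differ. Section {11b} argues this for (a), because the abdominal phase is the same in both arms, and then carries the argument over to (b). Nothing in the article confines (b) to the abdominal phase. In the chest one arm has a thoracotomy and the other minimally invasive access, and the surgeon knows the allocation ({17a}). The minor-surgery and equal-distribution arguments are no longer secure there.

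**Working it through.** **1. The plan's own figures.** Sample size {14} uses a difference of 10, SD 20, two-sided alpha 0.05 and 80% power. The t-test gives 63.8, so 64 per arm and 128 in total (power 80.1%). Loss of 15% (10% intraoperative, 5% other) gives 128/0.85 = 150.6, hence 151, or 152 with equal arms. The figures reproduce, so the point is not an arithmetic error. The 10% is 0.10 × 152 = 15.2 patients and leaves 0.90 × 76 = 68.4 per arm before other losses.

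**2. Who is in and who is out.**

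| Patient | Estimand | {11b} | {20a} read literally |
|---|---|---|---|
| Criterion (a), no resection | out | out | out |
| Criterion (b), no resection | out | out | out |
| Conversion to open surgery | in | in | in |
| Abdomino-cervical oesophagectomy | in | in | in |
| Transhiatal extended gastrectomy | in | in | **out** |
| Intraoperative death before resection | in, grade V | not addressed | **out** |
| Randomised, never operated on | meets neither (a) nor (b) | not addressed | **out** |

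The first four rows agree and the next two conflict. The last row is unresolved, because a score counted from surgery has no starting day for these patients.

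**3. The exclusion is described in three ways.** Section {14} begins with a decision not to resect the tumour. Below Fig. 1 it describes no oesophagectomy because of intraoperative findings. Section {20a} requires that oesophagectomy took place. An extended gastrectomy is a tumour resection, so it is not a drop-out where the test is a decision not to resect, but it can be one under the other two descriptions.

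**4. Does another planned analysis bring these patients back?** The per-protocol and as-treated sets in {20b} do not. The imputation in {20c} fills in missing values and does not restore excluded patients. Secondary endpoints, including 90-day mortality and serious adverse events, use the mITT and as-treated sets.

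**5. When criterion (b) is decided.** Abdominal Step 1 requires a resectability judgement at abdominal access but does not say that it is final. Thoracic Step II still deals with disease extent (left pleural resection in advanced disease to obtain a clear margin). A later decision under (b) is therefore neither described nor ruled out.

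**6. Illustration only.** The documents give no index values for excluded patients and no imbalance between arms, so both are assumed here. If one arm loses k more patients than the other, each D points above the mean of the n = 68 retained, the mean difference moves by k × D/(n + k).
- k = 2, D = 20: 40/70 = 0.57.
- k = 4, D = 40: 160/72 = 2.22.
- One omitted death scored at the scale maximum of 100, with a retained mean of 20 to 40: 80/69 = 1.16 down to 60/69 = 0.87.

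For comparison, the standard error is 20 × √(2/64) = 3.54 and the target is 10. A 2-point shift under the null would raise the two-sided type I error from 5% to about 8.7%. If excluded patients score below the retained mean, D is negative and the shift reverses. Equal losses of similar patients in both arms cancel.

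**The case against.** Most of the restriction is consistent with the estimand. The intraoperative exclusions are written into the population and repeated under intercurrent events, and {20a} can be read as shorthand for everyone who is not an intraoperative drop-out. The intent for the disputed patients is stated elsewhere: other operations stay in the trial, and intraoperative deaths are grade V. The resectability judgement is mandatory in the shared phase, and the protocol expects minor surgery in the excluded cases. Intraoperative deaths are also documented and reviewed by the data and safety monitoring board. The statistical analysis plan is not shown and may define the sets more fully.

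Much of this stands. A reader might infer that the whole mITT contradicts the estimand. It does not, because removing patients under (a) and (b) is part of the estimand. A reader might also infer that patients will be excluded from the chest phase unequally by arm. The article reports no such case and gives no frequency. The 15 expected drop-outs cover all non-resections, including those under (a), and should not be read as 15 wrongly excluded patients.

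The conflict in wording remains. Section {20a} fixes the confirmatory set in this document, says it matches the estimand, and does not name the exceptions that the other sections require. Safety review of a death does not place it in the primary analysis.

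**Conclusion.** The point holds in a limited form. As written, {20a} leaves out intraoperative deaths before resection and extended gastrectomies, which the estimand and {11b} count, so the stated correspondence is not exact. The article gives no rate for either group, and both are probably small. The exclusions under (a) and (b) agree with the estimand. The reasons given for (b) are secure only for findings made in the abdominal phase.

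Bias from a late, unblinded decision is possible, not shown. The shifts of 0.57 to 2.22 points rest on assumed imbalances and assumed scores, stay below one standard error, and could go either way. They do not support a conclusion that the confirmatory analysis is invalid. They do show that a few patients can matter enough to justify an exact definition. The drop-outs' outcomes should also be recorded prospectively, since they may not be recoverable later.

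**What to change.** 1. In {20a}, define the mITT as all randomised patients except those meeting criterion (a) or (b), analysed as randomised. State that intraoperative deaths and other resection types are included, and say how randomised patients who are never operated on are handled. Reconcile {11b}, Population, Intercurrent events, both drop-out descriptions in {14}, and {20a}.

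2. Record the operative phase and the reason for each intraoperative drop-out, and report both by arm.

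3. Record the 30-day comprehensive complication index and 90-day mortality and serious adverse events for intraoperative drop-outs. Rerun the primary model in all randomised operated patients as a supplementary analysis.

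If unresectability found in the chest is to stay in the primary set, criterion (b) in {10} and the estimand population must be amended to match. Otherwise the change creates a new mismatch.

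**Cost.** Wording changes and short follow-up of about 15 patients who have already consented. The primary analysis should lose almost no power, because 152 already allows for 15% loss and the restored patients add to the set. The supplementary estimate is diluted. If the 10% not resected had equal scores in both arms, a 10-point difference would become 0.90 × 10 = 9. With SD 20 and 0.95 × 76 = 72.2 per arm, power would be about 77%, which is acceptable for a supplementary analysis.

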**Methods:**

The MICkey trial is a multicentre randomized controlled superiority trial with two parallel study groups. A total of 152 patients with oesophageal cancer scheduled for elective oesophagectomy will be randomly assigned 1:1 to the control group (HYBRID-E) or to the intervention group (MIN-E). The primary endpoint will be overall postoperative morbidity assessed via the comprehensive complication index (CCI) within 30 days after surgery. Specific perioperative parameters, as well as patient-reported and oncological outcomes, will be analysed as secondary outcomes.

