### Methods in analysis to handle protocol non-adherence and any statistical methods to handle missing data {20c}

In the primary analysis, missing data are assumed to be at least “missing at random” and will be replaced using multiple imputation using the fully conditional specification method [16] and predictive matching taking the variables treatment group, age, comorbidity index, ASA status, neoadjuvant treatment, tumour type and tumour stage.

Due to the nature of the primary endpoint and the short evaluation period, missing data in the primary endpoint model is assumed to be very rare. Therefore, no sensitivity analyses regarding the imputation method and the underlying assumptions will be performed.

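### The primary model is valid, but pre-specifying ASA status, comorbidity index and neoadjuvant treatment beside age would be a cheap and probably modest gain in precision

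*Protocol article*

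**What the plan says.** Section {20a} fixes the confirmatory model: the CCI is compared "using a linear mixed model including treatment group and adjusting for age as a fixed effect, as well as center as a random effect". Section {16a} makes centre the only stratification factor, so the random effect matches the design. The estimand section defines the summary measure as the difference in mean CCI.

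Section {20c} imputes missing primary-endpoint data "taking the variables treatment group, age, comorbidity index, ASA status, neoadjuvant treatment, tumour type and tumour stage". Section {20b} also lists neoadjuvant therapy as a subgroup factor.

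The sample size section {14} rests on an unadjusted t-test. It states that "a decrease of the CCI by 10 points is considered relevant by patients and clinicians" and that "a conservative standard deviation of 20 is assumed", and it finds 64 per group enough "to achieve a power of 80% to reveal this difference". It adds that the mixed model should have at least the power of the t-test. No section says how strongly any baseline variable predicts the CCI, or why age alone was chosen.

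**The concern.** Three variables describing a patient's condition before surgery are planned for imputing the CCI but are absent from the model that carries the conclusion. In a linear model, covariates measured before randomisation and fixed in advance do not change what is estimated. If they predict the outcome, they reduce the residual variance and so the width of the confidence interval.

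The target is met with a small margin: 152 × 0.85 = 129.2 evaluable patients against 128 needed. At stake is therefore some precision in the primary mean difference, obtainable without new data. The validity of the trial is not at stake.

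**Working it through.** **Inputs from the protocol article.** Difference 10 points, SD 20, two-sided 5%, power 80%, 64 per group ({14} and {20a}); 1:1 allocation (abstract); 15% total drop-out ({14}).

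**Inputs assumed.**
- R², the share of CCI variance explained by the three covariates beyond age and centre. The documents give none; the range taken is 0 to 0.20.
- k, the number of added parameters: 3 if each variable takes one term, 5 if some enter as categories.
- The SD of 20 is treated as the residual SD of the current model, so any gain from age and centre is left out of both sides of the comparison.

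**Step 1: reproduce the plan.** Standardised difference 10/20 = 0.5. The noncentral t calculation gives 63.8, hence 64 per group, with power 80.1%. Then 128/0.85 = 150.6, hence 151, or 152 with equal groups. Both stated figures reproduce, and no covariate is needed to reach 80%.

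**Step 2: gain before any cost.** The residual SD becomes 20 × √(1 − R²). For R² = 0.10 it is 18.97. The standard error is 18.97 × √(2/64) = 3.354, against 20 × √(2/64) = 3.536 now. The approximate 95% half-width falls from 6.93 to 6.57 points.

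**Step 3: charge for the added parameters.** With 128 patients, fitting k extra terms inflates the variance of the treatment effect by about 125/(125 − k) and lowers the error degrees of freedom from 126 to 126 − k. Hence SE = 20 × √(1 − R²) × √(2/64) × √(125/(125 − k)). For R² = 0.10 and k = 3 this is 3.354 × 1.0122 = 3.395, and power is 83.2%.

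| Assumed R² | Power, no cost charged | Power, k = 3 | Power, k = 5 |
|---|---|---|---|
| 0 | 80.1% | 79.2% | 78.5% |
| 0.02 | 80.9% | 80.0% | 79.3% |
| 0.05 | 82.1% | 81.2% | 80.5% |
| 0.10 | 84.1% | 83.2% | 82.6% |
| 0.15 | 86.1% | 85.2% | 84.7% |
| 0.20 | 88.1% | 87.3% | 86.7% |

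**Step 4: break-even.** The standard error is unchanged when (1 − R²) × 125/(125 − k) = 1, that is R² = k/125. This is 0.024 for k = 3 and 0.04 for k = 5. If the covariates explain nothing, the loss is 80.1 − 79.2 = 0.9 points (k = 3) or 80.1 − 78.5 = 1.6 points (k = 5).

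**The case against.** The strongest reply is that nothing here is wrong. The model is pre-specified, includes the stratification factor, estimates the stated summary measure without bias and reaches 80% power on the protocol's own inputs. All of that stands.

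A reader might go further than the documents allow in four ways:

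- **That precision is given away for nothing.** The gain depends on an R² that the documents do not report, and the extra terms have a small cost. Eligibility {10} excludes ASA grade above 3 and advanced cirrhosis, which may limit what ASA and comorbidity can explain.
- **That {20a} and {20c} conflict.** An imputation model richer than the analysis model is legitimate. Variables may enter it because they relate to missingness, so their listing does not show that the plan regards them as strong predictors of the CCI.
- **That the design has no slack.** The SD is described as conservative, and the drop-out allowance already protects the 128. Operated patients with a missing CCI are imputed rather than dropped. If only the 10% intraoperative drop-outs leave, 152 × 0.90 = 136.8, about 68 per arm, with power 82.5%. That is an upper bound, because imputation does not restore all lost information.
- **That chance imbalance in ASA or comorbidity is a flaw.** Under randomisation it is already covered by the type I error and the confidence interval, and it does not bias the comparison.

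The reply does not remove the suggestion itself. The protocol fixes the covariates of the primary model, so the choice is not one it leaves open, and no reason for age alone is given.

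**Conclusion.** The point holds as a low-cost improvement in precision, not as an error, a contradiction or a threat to validity. With 64 per arm, and after paying for 3 to 5 parameters, power would rise from 80.1% to 80.5–81.2% at an assumed R² of 0.05, 82.6–83.2% at 0.10 and 84.7–85.2% at 0.15. Below an R² of about 0.02 to 0.04 there is no gain.

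The trade is favourable because the possible loss is small and bounded while the plausible gain is somewhat larger. It rests on the assumed R² range, on the protocol's SD and difference, and on the three variables being available before randomisation. ASA must be known for eligibility. That the comorbidity index and neoadjuvant treatment belong to the baseline clinical data of visit 1 is an assumption, because the timeline does not list them by name.

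**What to change.** In {20a}, and in the analysis plan before database closure, add ASA status, comorbidity index and neoadjuvant treatment (yes/no), all as recorded before randomisation, as fixed effects beside age, with centre still random. State the coding, with as few parameters as possible: for example one term for the comorbidity index, and ASA as one linear or binary term. Keep the age-only model as a sensitivity analysis. If the trial team prefers age alone, give the reason in one sentence.

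The imputation list in {20c} already contains these variables and needs no change for this purpose. Tumour stage should join the primary model only as clinical stage, because the timeline records histopathology at the surgery visit, after randomisation.

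Cost: a change of wording, no new data if the variables are collected as {20c} implies, 3 to 5 parameters, and at worst about 1 to 1.6 points of power.
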